## **10.0 Quality Control and Quality Assurance**

To continuously evaluate the fidelity of both conditions, the PIs will review written logs maintained by the pharmacists and HCs that include visit dates, length of visits, visit content, and disposition (e.g., visit completed, patient unreachable, etc.). Weekly group meetings with HCs and PIs provide an opportunity to monitor the intervention delivery and on-going training. All technology-related difficulties are reported to the coordinator immediately and discussed in weekly meetings with the PIs. [name] will maintain weekly involvement with HCs to provide support and incorporate structured training opportunities quarterly. Additionally, [name] will maintain weekly involvement with research personnel to provide support and incorporate structured training opportunities for the sub-study data collection and equipment retrieval.

## **11.0 Data and Safety Monitoring**

The Data and Safety Monitoring Plan (DSMP) for the proposed project has two goals: (1) to insure the safety of the participants; and (2) to produce high quality research while considering both risks and benefits. Overall, the study poses minimal risk to participants. Because of this low risk status, the DSMP focuses on close monitoring by the co-principal investigators (co-PIs) and a safety officer (SO), along with prompt reporting of excessive adverse events and any serious adverse events to the NIH and to the IRB at the University of Illinois at Chicago (UIC).

Although there are additional reports to be produced by the study coordinator as a result of this DSMP, there are no substantive changes to the study protocol that might require review by the NIH. Safety reports will be sent to the study statistician, the co-PIs, and the SO. A research assistant will be responsible for assembling the data and producing these reports, as well as assuring that all parties obtain copies of these reports.

The research team will meet weekly and continuously evaluate the progress of the trial, including periodic assessments of data quality and timeliness, participant recruitment and retention, participant risk versus benefit, subject complaints (if any), adverse events, and other factors that can affect study outcomes. Summaries of enrollment and withdrawals will be reviewed together.

The frequency of data review differs according to the type of data as follows:

| Data Type               | Frequency of Review         |
|--------------------------------|------------------------------------|
| Subject enrollment             | Quarterly during recruitment phase |
| Subject status (retention)     | Biannually                         |
| Adverse event rates (injuries) | As they occur                      |

*Qualifications and Responsibilities of the Safety Officer:* We will identify an independent safety officer (SO) for this trial. This individual will have an advanced medical degree and experience in human subject protection, research study design, and the adverse event review process. The safety officer will review the reports sent by the study coordinator (at the frequency outlined above in the table) and will use a checklist to determine whether there is any corrective action, trigger, or an ad hoc review that should be communicated to the study investigator, the UIC IRB, and the NIH.

*Reporting of Subject Accrual, Adherence to Inclusion/Exclusion Criteria:* Review of the rate of subject accrual and adherence to inclusion/exclusion criteria will occur monthly during the recruitment phase by the co-PIs, SO, and the statistician. *Reporting of Adverse Events:* The research staff will be asked to report any problems the participants experience to the co-PIs either in person or by telephone. The safety officer (SO) will review, collate, and evaluate adverse events in real-time. Any adverse events reported to the IRB will also be reported to the NIH. All adverse events will be evaluated by the SO and the co-PIs within 72 hours; serious adverse events within 24 hours. Any study-related serious adverse event will be reported to the UIC IRB within 24 hours and the NIH within 2 weeks; all others will be included in the annual report to the NIH.

*Data Privacy and Security:* Formal training on data and participant safety is provided to all research staff involved in the data collection process, including health coaches. All staff and students involved in our research studies sign a confidentiality agreement stating that they are aware that any data they come in contact with is strictly confidential and is not to be discussed outside of the research project. They also complete the University of Illinois at Chicago online training on Human Subjects Protection (101) and the HIPAA Privacy Act. This will include the various modes of communication (e.g., telephone) and methods of maintaining confidentiality. At the UI Health and UIC research offices, all workstations require the use of a password in order to gain access. When leaving a workstation unattended, the user must log-out or lock their computer. Users are required to use screen savers that will be activated after ten minutes of inactivity and are password protected. All correspondence via fax must be stripped of patient identifiers. Before receiving a fax containing sensitive data, the sender must call the receiver to ensure the receiver is available to pick up the data. All e-mail with e-PHI will be sent securely through Cisco's Registered Envelope Service (CRES). The coding system will be kept in a locked cabinet or drawer separate from the actual data. Research investigators performing the statistical analyses data will not have access to information that can connect up the actual identity of a study participant and their data. Information connecting a study participant's name and study identifying number is kept in a locked file drawer in one of the co-PI's office.

*VSee videoconferencing* uses “peer-to-peer” sessions so information is not stored on a VSee server. VSee uses 256-bit AES (Advanced Encryption Standard) for secure transmission of information. Text messaging will not be secure and will not contain e-PHI. However, *mytapp* includes multiple security measures. Limited subject information will be available on *mytapp*, such as name and study ID number, and telephone number stored in an encrypted PostgreSQL database. We utilize TLS (Transport Layer Security) with encryption for all *mytapp* interactions and interactions with Twilio. All information from Twilio to *mytapp* is validated against embedded digital signatures to ensure authenticity and prevent “spoofing.” A “PaperTrail” application provides a continuous audit trail to monitor *mytapp* use and all message activity. We will utilize a comprehensive approach to maximize privacy and data security for videoconferencing and text messaging services. We will include an information privacy and security committee to advise, assist, and monitor our research policies using technology and for documentation. The committee will include an IT security expert, privacy official, and a clinician from UI Health. The committee will: (1) conduct a formal risk analysis; (2) develop a risk management strategy based on risk analysis; (3) implement strategy and assist in training staff; and (4) monitor risk continuously.

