### **6.1 Overview of Participant Procedures**

#### Recruitment and Randomization

1. Potential participants will be identified by one of four recruitment methods previously described.
2. RAs will screen patients for eligibility and discuss the study protocol in detail. If the patient is deemed eligible to participate he/she will complete written informed consent and HIPAA authorization.

3. Enrolled participants will schedule an appointment at the UIC Clinical Interface Core (CIC) to complete baseline data collection, which includes a blood draw.
4. Participants randomized to *mDAS* will receive the intervention component in Year 1, while participants randomized to *Usual Care* will receive it in Year 2. RAs will inform participants of assignment.

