*Health Coaches.* The study includes both African-American and bilingual/bicultural Latino health coaches representative of the communities they serve. All of our current HCs are the first person in their families to earn an undergraduate college degree, come from low-income backgrounds, and recognize the importance of cultural-based norms. All HCs have an undergraduate degree in or related to Community Health with experience conducting home visits. They receive 80 hours of standardized training/retraining beginning with diverse Latino and African-American cultures in America and the influence of poverty upon health. HCs provide culturally sensitive support and tailor based on participant personal preferences. Fundamental education in diabetes includes the Diabetes Education Empowerment Program

(DEEP) targeting literacy and cultural awareness and [name] Training Curriculum for Health Coaches. HCs shadow a clinical pharmacist to understand medication use, adherence, glucose and blood pressure monitoring, insulin injection, and medication reconciliation. On-going training is provided every two months on related topics that reinforce and expand the initial training. We provide training in videoconferencing (e.g., scheduling and practice encounters), text messaging (e.g., text application practice and standardized safety procedures), and conducting home visits in a culturally sensitive manner. HCs receive routine orientation to clinical operations and staff at their primary care locations. Standardized safety procedures related to text messaging and home visits are also addressed. [name], a consultant, provides training in motivational interviewing related to adherence. To evaluate clinical skills, the HCs will demonstrate reliable measurement of blood sugar, blood pressure, pulse, and administration of insulin (though HCs do not administer insulin to patients).

The HC component involves monthly home visits with on-going telephone support. Every other month a visit will include facilitation of the pharmacist videoconference, with the patient spending an additional time with the HC afterwards for reinforcement. HC visits including pharmacist videoconferencing will last 60-90 minutes total, while the HC visits without pharmacist involvement will last 30-45 minutes.

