*Extreme Blood Sugar or Blood Pressure Levels:* If a patient takes too much or too little medication, blood sugar and blood pressure levels may be too low or too high. The expected frequency of experienced side effects among participants is comparable as those receiving usual care taking the same medication. However, greater intensification of therapy could potentially increase this risk. To minimize risk, pharmacists and PCPs follow standard algorithms for glycemic and blood pressure management (i.e., American Diabetes Association and Joint National Committee on Prevention, Detection, Evaluation, and Treatment of High Blood Pressure) and use standard precautions in adjusting therapy: (1) addressing side effects (e.g., hypoglycemia) during every patient contact; (2) applying principles of aggressive therapy (education, empowerment, self-monitoring, flexible medication regimen, individualized goals, professional guidance); and (3) considering risk factors for hypoglycemia or hypotension. HCs also receive specific training on how to respond to extreme blood sugars and blood pressures if this occurs during a visit. They will be trained to respond in manner that is appropriate for their positions as trained lay-people.

Currently, at least one-third to two-thirds of patients with diabetes do not take their diabetes and hypertension medications correctly. In contrast, study participants will receive greater monitoring and support than other patients receiving usual care, which may help them

take medication more properly. The study procedures will allow for medication adjustment in a logical, conservative fashion, whereas many patients may adjust therapies on their own, or with infrequent or ineffective provider contact, not adjust at all. All pharmacists and health coaches receive extensive training and monitoring to deliver appropriate assistance to patients. We have implemented additional protection with PCP (or covering physician) contact if necessary at any time, day or night. Based on the frequent contact and monitoring involved, participants have less extreme blood sugar or blood pressure levels than those receiving usual care.

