*Poor Information:* It is possible that subjects may receive and act on inaccurate information or misinterpret accurate information given the team approach and novel communication methods utilized. However, it remains more likely that there is a greater risk of misinformation from providers when additional support is not available, especially due to language and cultural barriers. To address this, HCs receive training and ongoing evaluation to reduce the risk of providing misinformation. HCs serving Latino patients will be bilingual, and all communication as well as informational materials will be in either English or Spanish to avoid a potential language barrier. In addition, HCs work closely with pharmacists and communicate regularly, providing a means to obtain accurate information and receive prompt and clear answers to their questions. To address any possibility for subject concern regarding information received, we will encourage them to seek help from their primary care physician (PCP) and pharmacist if they are uncomfortable with any of the information provided by health coaches.

*Breach of Confidentiality:* There is a small risk of breach of confidentiality, regarding health information and collected research data. All research staff, including pharmacists and HCs, will have formal IRB human subject protection and HIPAA training. Additional HC training includes discussions on maintaining confidentiality of health information, including communication with health providers. For data collection, all subjects will be assigned a blind code number. These lists will be kept in a locked file and will not be shown to staff. Data collected from computer use files will have the name removed and the code number attached by the research coordinator. Project staff who have access to the data will not have access to subject names. No clinical staff who have direct contact with the subjects will have access to research data. Finally, there will be no personal information stored on the server itself; and all e-mail communication will be encrypted and secure.

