*Videoconferences* will be conducted through VSee. VSee provides real-time person-to-person audio and video communications. It is most suitable for health-related communication, as it is FDA registered and HIPAA compliant. VSee uses 256-bit AES (Advanced Encryption Standard) and “peer-to-peer” sessions so information is not stored on a VSee server. Although VSee allows for local file storage which may be considered electronic personal health information (e-PHI), UI Health does not currently have electronic storage of such communications into the electronic medical record. Pharmacist notes abstracting the relevant details of the videoconference encounter will be recorded in the medical records. Overall, the risk of accidental disclosure of e-PHI is very small.

*Text messages* will not include any identifying information nor will any personal health information be disclosed by our team. Patients will be instructed not to use text messaging to share health information. Patients will be reminded that text messages are sent in an automated fashion by computer. Thus, any replies may not be read in a timely fashion. Text

messaging by patients should not be considered an Emergency Response System. Furthermore, they will be told and reminded that urgent health questions should be directed to their physician and not sent in a text message. If an individual does share e-PHI through text messaging, the information will be permanently deleted and the patient will be educated regarding this process.

*Feeling annoyed by text messages:* Subjects will receive regular scheduled text messages during the study. Participants who no longer wish to receive reminders or text messages may reply with “STOP.” Twilio automatically will block *mytapp* from sending messages if this is received; thus, messages will be immediately discontinued without requiring contact with research team. However, patients have the option to re-subscribe with “START” again and resume messages. *mytapp* also color-codes blocked messages as “red” which will be easily detected by health coaches. This allows the HCs to identify problems including loss of mobile service.

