**Table 4: RE-AIM Framework for Process Evaluation**

|                       |                                                                                                                                                                                                                                                                                    |
|-----------------------|------------------------------------------------------------------------------------------------------------------------------------------------------------------------------------------------------------------------------------------------------------------------------------|
| Reach          | Identify proportion of eligible population contacted, responded, participated, and excluded. Compare demographics and glycemic levels of eligible UI Health patients and study participants. Are the study participants representative of the clinical population?                 |
| Effectiveness  | Determine change in hemoglobin A1c, blood pressure, and other outcomes (Aim 1). Are there unintended consequences of the intervention (e.g., negative impact on quality of life)?                                                                                                  |
| Adoption       | Conduct semi-structured interviews with randomly selected providers, staff, administrators, and health coaches across participating clinical sites (interview guides to be developed). Assess satisfaction and compare resources, setting, and intervention delivery across sites. |
| Implementation | Measure HC activity including encounters and phone calls completed, videoconferencing, and text messages delivered. Determine subject participation in intervention.                                                                                                               |
| Maintenance    | Implement Sustainability Action Plan (Aim 2). Evaluate change in outcomes one year after completion of the intervention and determine if positive outcomes were maintained. Assess drop-out rates and adverse events experienced.                                                  |

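### Adverse events are collected without structure and with unequal contact between arms, so reported rates of non-severe hypoglycaemia and between-visit symptomatic hypotension are open to detection bias

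*Protocol*

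**What the plan says.** **Intake.** Protocol Section 11.0 (Reporting of Adverse Events) states: "The research staff will be asked to report any problems the participants experience to the co-PIs either in person or by telephone". The safety officer then reviews and collates events. All adverse events are to be evaluated within 72 hours and serious ones within 24 hours.

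**Who reports.** Section 7.0 counts the interventionists among research staff: "All research staff, including pharmacists and HCs, will have formal IRB human subject protection and HIPAA training". Research assistants, who interview every participant, also belong to that group.

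**Who is seen, and when.** Section 6.1 (Recruitment and Randomization) says mDAS participants "will receive the intervention component in Year 1, while participants randomized to" usual care receive it in Year 2. Section 6.4 adds: "The HC component involves monthly home visits with on-going telephone support". Pharmacist videoconferences take place during coach visits. Both arms attend data collection at 6, 12, 18 and 24 months.

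**Named risk.** Section 7.0 puts blood sugar or blood pressure that is too low or too high first among the main risks, and says that "greater intensification of therapy could potentially increase this risk". Sections 6.4 and 7.0 describe raising hypoglycaemia at patient contacts, in the setting of pharmacists and primary care physicians managing therapy.

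**Review and later use.** The adverse-event row of the Section 11.0 table reads "Adverse event rates (injuries"), with review as events occur. Table 4 (RE-AIM) asks about unintended consequences under Effectiveness and, under Maintenance, plans to "Assess drop-out rates and adverse events experienced".

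**The concern.** How well an event is captured depends on how often, and by whom, the patient is asked. Here both follow treatment assignment. A patient on mDAS in Year 1 is asked about low glucose by people whose job includes asking. A usual-care patient mentions it, if at all, to a research assistant at a six-monthly interview for which no such question is listed.

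This matters because the protocol itself says intensification may raise the risk. In the same section it goes on to say that participants have less extreme blood sugar or blood pressure than patients in usual care. For mild and between-visit events, the data as collected cannot separate these possibilities well. An apparent excess on mDAS could be an artefact of closer contact, and a true excess could be dismissed as one. In Year 2 the distortion runs the other way. No later analysis can recover events that nobody recorded.

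**Working it through.** **1. Contacts in Year 1 (after baseline).** Inputs: monthly coach visits (Section 6.4) and data collection at 6 and 12 months (Section 6.1, Data Collection).

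- mDAS: 12 + 2 = 14. Pharmacist videoconferences fall within coach visits and add none.
- Usual care: 2.
- Ratio: 14 / 2 = 7.

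The count leaves out calls and texts to mDAS patients, retention calls, which are not restricted to an arm, and the usual-care referral to an educator and clinical pharmacist. It compares opportunities to report. It is not a ratio of detection.

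**2. What each source covers.**

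| Source | Both arms alike? | What it can capture |
|---|---|---|
| Coach and pharmacist contacts (6.4) | No: mDAS in Year 1, usual care in Year 2 | Any problem; hypoglycaemia is raised |
| Coach worksheet with self-monitored glucose and blood pressure (8.0) | No: only those then on mDAS | Home readings |
| Blood pressure by blinded staff, extreme values escalated (8.0) | Yes | Blood pressure at the visit only |
| Admissions, emergency and outpatient use (8.0, Cost and Healthcare Utilization Data) | Yes | Events that led to care |
| Research assistant interview (6.1, 8.0) | Yes | No hypoglycaemia or symptomatic-hypotension item is listed |

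Non-severe hypoglycaemia and symptomatic hypotension between visits have no row that is both common to the arms and designed to find them. The healthcare-use data are collected for costing, and no route from them to the safety officer is stated. Under the temporary COVID-19 changes, surveys move to the telephone and home kits are offered for A1c and cholesterol, with no replacement stated for blood pressure. Section 12.0 explores the consequences of intensification through BMI and quality of life, not through these events.

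**3. Illustration of size.** The protocol gives no event rate, margin or safety power, so there is no stated figure to reproduce. Assume 110 per arm (220 / 2, equal allocation), the same true risk p in both arms, and detection s1 on mDAS and s0 in usual care.

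- Reported patients per arm = 110 × p × s.
- Apparent risk ratio = (p × s1) / (p × s0) = s1 / s0, whatever p is.
- Chance of a spurious significant excess on mDAS (two-sided 5% test of two proportions) = Φ[(d − 1.96 × SE0) / SE1]. Here d is the difference in reported proportions, SE0 the pooled and SE1 the unpooled standard error.

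Worked case, p = 0.20, detection 0.9 v 0.5: reported proportions 0.18 and 0.10; d = 0.08; SE0 = √(0.14 × 0.86 × 2/110) = 0.0468; SE1 = √((0.18 × 0.82 + 0.10 × 0.90)/110) = 0.0465; Φ(−0.25) = 0.40.

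| True risk | Detection | Reported patients | Apparent ratio | Chance of spurious significance |
|---|---|---|---|---|
| 10% | 0.9 v 0.7 | 9.9 v 7.7 | 1.29 | 0.08 |
| 10% | 0.9 v 0.5 | 9.9 v 5.5 | 1.80 | 0.21 |
| 10% | 0.8 v 0.3 | 8.8 v 3.3 | 2.67 | 0.37 |
| 20% | 0.9 v 0.7 | 19.8 v 15.4 | 1.29 | 0.13 |
| 20% | 0.9 v 0.5 | 19.8 v 11.0 | 1.80 | 0.40 |
| 20% | 0.8 v 0.3 | 17.6 v 6.6 | 2.67 | 0.66 |
| 30% | 0.9 v 0.7 | 29.7 v 23.1 | 1.29 | 0.18 |
| 30% | 0.9 v 0.5 | 29.7 v 16.5 | 1.80 | 0.59 |
| 30% | 0.8 v 0.3 | 26.4 v 9.9 | 2.67 | 0.86 |

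Every true risk and detection rate here is an assumption. The table shows how unequal detection would act, not how large it is in this trial.

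**4. The table row against the text.** The row is labelled as injuries. The paragraph on reporting covers all adverse events, and Section 7.0 names glucose and blood pressure as the main risk. These passages do not agree.

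**The case against.** The strongest reply is that Section 11.0 is there to protect participants in a study described as minimal risk. Closer surveillance where therapy is intensified serves that purpose, and no between-arm test of adverse events is planned. Much of that stands: the point concerns interpretation of the data and does not show that safety oversight fails. Even so, Table 4 will draw on these data, and Section 7.0 makes comparative statements about this risk.

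A reader might also infer four stronger things, none of which the documents support:

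- *Events arrive mainly through coaches and pharmacists.* The text says research staff, and research assistants see both arms.
- *The named risk cannot be compared at all.* Blood pressure by blinded staff and emergency or hospital use are collected in both arms, so visit extremes and events leading to care can be compared.
- *Review cannot reveal an excess.* The safety officer collates events, the team weighs risk against benefit at weekly meetings, and the row itself speaks of rates.
- *Texted reports are lost.* Section 7.0 does say "If an individual does share e-PHI through text messaging, the information will be permanently deleted", but this does not cancel the duty to report problems. Coaches and the coordinator also monitor replies, and coaches summarise patient communication in the medical record.

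It is also fair to say that seven times the contact does not mean seven times the detection, since a six-month interview can pick up earlier events.

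**Conclusion.** The point holds in a limited form, as a cheap improvement. Adverse-event ascertainment is unstructured and unequal between arms, at about 14 against 2 scheduled study contacts in Year 1 and reversed in Year 2. Reported rates of non-severe hypoglycaemia and between-visit symptomatic hypotension are therefore open to detection bias. Severe events that lead to care, and blood pressure at visits, are largely outside the problem.

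The conclusion rests on the listed measures being complete for the interviews both arms attend. The direction of the bias in Year 1 is towards an apparent excess on mDAS; its size is unknown. The injuries label is an inconsistency to reconcile, not proof that other events go unreviewed.

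**What to change.** 1. Add one identical block to the research assistants' interview at 6, 12, 18 and 24 months in both arms. It should ask about low-glucose and low-blood-pressure events, and any care sought for them, since the last visit.
2. Base any between-arm adverse-event summary on that block plus the medical-record, billing and healthcare-use data already collected under Section 8.0. Keep coach and pharmacist reports for action on individual safety.
3. Reconcile the injuries label in the Section 11.0 table with that section's coverage of all adverse events and with the risks named in Section 7.0. Give the safety officer a by-arm count at the biannual review the table already schedules for retention, and keep review of single events as they occur.

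Cost: a few minutes in an interview of about 60 minutes, one more table in a periodic report, and a protocol amendment. Six-month recall is imperfect and may differ by arm, because mDAS patients are taught about hypoglycaemia and know their assignment. The block reduces the bias without removing it, which is why it is paired with record-based data.
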